# How can the utilisation of help for mental disorders be improved? A quasi-experimental online study on the changeability of stigmatising attitudes and intermediate variables in the process of utilisation

**DOI:** 10.1186/s12889-021-12125-5

**Published:** 2021-11-19

**Keywords:** Mental health, Help-seeking behaviour, Depression, Continuum belief of mental illness, Causal beliefs, Mental health literacy, Self-efficacy, Anti-stigma intervention, Quasi-experimental online-study

## Abstract

**Background:**

Epidemiological studies show that even in highly developed countries many people with depression do not seek help for their mental health issues, despite promising prevention approaches encouraging people to seek help and reduce self-stigma. Therefore, an anti-stigma intervention study to support help-seeking behaviour will be developed on the basis of the newly explicated “Seeking Mental Health Care Model”.

**Methods:**

A quasi-experimental online study will be carried out to assess the effect of different intervention variables relevant for the help-seeking process. The study is conceived as a fractional factorial design. Participants will be screened for depressive complaints (PHQ-9 sum score ≥ 8) and current psychiatric/psychotherapeutic treatment. After baseline assessment the participants will be randomly allocated into one of the 24 study groups receiving different combinations of the vignette-based intervention aiming to reduce stigma and support help-seeking. Next, relevant outcome measures will be administered a second time. In a 3- and 6-month follow-up help-seeking behaviour will be measured. Gamified elements and avatar-choice techniques will be used to heighten study immersion and adherence.

**Discussion:**

On the basis of the project results, promising research and intervention perspectives can be developed. Results, firstly, allow for a more detailed empirical investigation and conceptualisation of the stages of mental health care utilisation, as well as an examination of theoretical approaches to stigmatisation. Secondly, our online study could provide insights for an evidence-based design and evaluation of online interventions for people with a mental illness.

**Trial registration:**

German Clinical Trials Register: DRKS00023557. Registered 11 December 2020. World Health Organization, Universal Trial Number: U1111–1264-9954. Registered 16 February 2021.

**Supplementary Information:**

The online version contains supplementary material available at 10.1186/s12889-021-12125-5.

## Background

Epidemiological studies show that even in countries with well-developed primary care and specialised mental health services most people with a mental illness do not seek treatment for their disorders, or only after considerable delay [6, 63]. In Germany two thirds of people with depressive symptoms do not seek mental health care [44]. This gap between health care need and utilisation exists despite modern developments in health promotion as well as selective preventive efforts such as mental health awareness campaigns. Moreover, people are systematically labelled and stigmatised for their mental illness [11, 38, 45]. People with a mental illness are often seen as dangerous, unpredictable, unreliable, and not normal [3]. The societal stigmatisation of people with a mental illness can be seen on many different levels, whether it is in personal day to day interactions, in working environments, on an institutional level, or in the media [11, 29]. A person with a mental illness who is aware of, agrees with, and internalises publicly endorsed stigmatising stereotypes, self-stigmatises and can experience loss of self-esteem, shame, and helplessness, inhibiting help-seeking behaviour [11, 47]. Therefore, it is important to address stigma in interventions supporting health care utilisation.

In a previous project the direct impact of stigmatising attitudes on help-seeking behaviour was examined. Results showed that stigmatising attitudes were negatively associated with a perceived need for help [59] and the use of professional psychiatric and psychotherapeutic help (β = − 0.19, *p* = 0.08). Furthermore, the main predictor for health care utilisation was the intention to seek help, which explained 22–37% of the variance of actual help-seeking behaviour and was especially strong for seeking psychotherapeutic help (β = 0.31, *p* < 0.001 [60];). Additionally, further findings concerning the self-identification as mentally ill [57], as well as a subjective sense of illness [58] and their respective association with help-seeking intention and behaviour were considered. On the basis of these findings it became evident that the working model had to be extended by one superordinate and five intermediary variables to account for the complex ways in which stigma impacts the help-seeking process. We use this extended and newly explicated model as the theoretical foundation of our present study.

According to the “Seeking Mental Health Care Model” (see Fig. 1) a person moves from becoming aware of their own psychological complaints, self-identifying as mentally ill, forming the intention to seek help (i.e., accepting that one needs help), to eventually seeking out professional help. On the superordinate level previous treatment experience [57] is added to stigmatising attitudes, as both influence the whole help-seeking process through their impact on the intermediary variables as well as their direct association with help-seeking behaviour. On an intermediary level, the following five variables are identified to have an impact on the help-seeking process and stigmatising attitudes respectively. *Continuum belief of mental illness*, the belief that there is a fluid transition between health and illness is associated with less stigmatising attitudes (e.g., [50]). *Mental health literacy*, the beliefs, attitudes, and knowledge concerning mental illness and the treatment thereof [25] is included, as studies point to its positive impact on the help-seeking process (e.g., [26, 53]). *Causal beliefs,* the subjective belief of the causes of the symptoms the person is experiencing is included. Studies show differential results of the effects of causal beliefs on stigma and help-seeking (e.g., [33, 57]). Finally, self-efficacy is included in the model, which we again specified as the (4) *self-efficacy to help oneself* and (5) *self-efficacy to seek out professional* help, since they seem to have a different effect on help-seeking intention and behaviour [60, 61]. The Common-Sense-Model of Self-Regulation (CSM [36];) is used as a corresponding theoretical framework. The CSM describes the subjective management of health threats, that is, how a person labels their symptoms (identity), rates the onset, duration, and fluctuation of them (timeline), attributes causal antecedents to their symptoms (cause), evaluates their perceived impact (consequence), treats the symptoms themselves (perceived control), and comprehends them (coherence). These six cognitive illness representations, which have been shown to have an impact on illness outcomes [21], are parallelised with the corresponding intermediary variables of our proposed model (see Fig. 1) to integrate the separate constructs into one holistic model (e.g., *coherence* is parallelised with the construct *continuum belief of mental illness*).

**Fig. 1 Fig1:**
[figure not shown]
Seeking Mental Health-Care Model. Note. This figure shows the process in which a person seeks out mental health-care, starting with a person becoming aware of their own psychological complaints. CSM = Common-Sense Model of Self-Regulation, parallelised cognitive illness representations. SE = Self-Efficacy

### Research agenda of the current study (stigma-II)

The present study will examine the effects of a short, informational, one-time administered intervention, aimed at influencing the intermediary process variables (i.e., continuum belief of mental illness, mental health literacy, causal beliefs, and self-efficacy to help oneself as well as seeking professional help) which in turn will reduce stigmatising attitudes and facilitate help-seeking.

The study will focus on people with at least mild depressive complaints, who are currently not receiving professional psychiatric/psychotherapeutic treatment, and live in Germany. Possible effects of the Covid-19 pandemic are assessed (e.g., adherence to regulations, mental-health burden through regulations), since it is assumed that the pandemic and lockdown-regulations had an impact on psychological well-being in general [14].

Participants of the experimental groups will receive a text-based vignette followed by a combination of online-administered interventional vignettes (either as a text and/or a video) designed to influence the five intermediary process variables described above. The participants of the control group will only be presented with the case-vignette. The primary and secondary outcomes will be measured directly pre- and post-intervention, as well as after 3 and 6 months in subsequent follow-up assessments. The primary outcome “help-seeking behaviour” will be assessed at the subsequent follow-ups. The study is designed as a quasi-experimental online study and the chosen design of experiment is the fractional factorial design [15] to adequately account for the complexity of all the possible intervention-combinations required to answer the research questions.

Prospectively, the study’s results will lead to a better understanding of the complex interplay between stigmatising attitudes and mental health care utilisation and which intermediary mechanisms play a pivotal role therewith. Moreover, the results could be used to design population wide prevention campaigns to encourage help-seeking when suffering from depressive complaints, on the one hand, and reduce stigmatising attitudes, on the other hand.

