#### Primary research questions

The intervention is expected to directly and indirectly influence help-seeking intention and behaviour positively, resulting in a higher intention as well as higher rates of professional health care utilisation. Our primary research questions are:
Does a biopsychosocial causal model of depression make it easier to articulate an intention to seek health care treatment?H1: The agreement with a biopsychosocial- vs. a mono-causal model leads to a higher help-seeking intention.Does the strengthening of context-specific self-efficacy (self-efficacy to help oneself and to seek professional help) influence treatment intention or utilisation?H2: Enhancing self-efficacy to help oneself leads to less intention to seek professional help (H2a), whereas enhancing self-efficacy to seek professional help leads to higher help-seeking intention (H2b) and help-seeking behaviour (H2c).What importance does previous treatment experience have for the development of both self-efficacies and the last stages of the process of help-seeking?H3: Positive treatment experience is associated positively with both self-efficacies (H3a), help-seeking intention (H3b) and behaviour (H3c).

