### Study information

#### Power & sample size

The required sample size is based on calculations for ANOVA (repeated measures, within-between interaction) expecting small effect sizes of *f* = 0.10 due to the limited intervention administration time and the online setting. A significance level of α = 0.05 and a power of *1-*β = 0.95, as well as the a priori determined 24 groups were included in the calculation. The free software G*Power [16] was used to calculate the required sample size of *N* = 840. This would mean *n* = 35 in each group. To stray on the side of safety we strive to recruit *n* = 40 for each group, a total of *N* = 960 participants, to complete the second follow-up after 6 months of intervention administration. Based on previous experience we estimate a drop-out rate of 47% between the first assessment time and the second follow-up 6 months later, we aim to recruit *N* = 1.800 at the beginning of the study (see Fig. 2).

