### Outcome measures

Table 2 shows the variables that will be investigated at different times during the study and the instruments used to assess these. They have been classified into general psychological, intermediary process, help-seeking, stigmatisation, and context assessment measures. The final selection of the instruments, some adapted to fit the current research setting, were based on theoretical research and pre-study test results (*N* = 227), in which psychometric properties, especially of the adapted instruments, were analysed.

**Table 2 Tab2:** Questionnaires employed at the different study assessment times

Study assessments & measures	Number of items	Study time points			
		T0	T1	T2	T3
Socio-demographic					
Gender	1	X			
Month& year of birth	2	X			
Family status & partner	3	X			
Education	2	X			
Employment	2	X			
Income	1	X			
General psychological					
Subjective general health (SF-1)	1	X		X	X
Quality of life (EUROHIS-QoL Index)	8		X	X	X
Self-construal Scale (SCS)	24	X			
Subjective Socio-Economic Status	1				X
Intermediary process					
Continuum beliefs (CB_new)	12	X	X	X	X
Causal beliefs (List)	18	X	X	X	X
Mental health literacy, depression specific (D-Lit)	12	X	X	X	X
Self-efficacy to help oneself	6	X	X	X	X
Self-efficacy to seek out professional help	7	X	X	X	X
Help-seeking					
Subjective sense of illness (B-IPQ-R)	9	X		X	X
Self-identification as mentally ill (SELF-I)	5	X	X	X	X
Attitudes towards help-seeking (ATSPPH-SF)	10	X	X	X	X
Motivation behind help-seeking (ACMQ)	6	X	X		
Help-seeking intention (List)	16	X	X	X	X
Help-seeking subjective norms, attitudes and perceived control (TPB)	10	X	X	X	X
Help-seeking behaviour/ health-care utilisation	18			X	X
Stigmatisation					
Perceived public stigma and the agreement with stigma (SSMIS-public & -self-SF)	10	X	X	X	X
Social distance stigma (SDS)	7	X	X	X	X
Discrimination of mental illness	3	X	X	X	X
Sense of blame for mental illness	4	X	X	X	X
Self-stigma for seeking out professional help (SSOSH-SF)	3	X	X	X	X
Shame for being mentally ill and seeking out help	2	X	X	X	X
Emotional reaction towards a person with mental illness (ERMIS)	10	X	X	X	X
Context					
Depressive Symptoms (PHQ-9)	9	X	X	X	X
Anxiety Symptoms (PHQ-anxiety module)	7		X		
Differential diagnosis	1		X		
Previous treatment experience	3–7		X		
Perceived availability and accessibility to the health care system	1–5		X		
Covid-19 questions	4	X		X	X
	∑ = 246				

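### The named primary outcome (help-seeking behaviour, follow-up only) does not match the stated timing, most of the primary hypotheses, or the repeated-measures power calculation

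*Protocol article*

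**What the plan says.** Three parts of the protocol article bear on what is primary.

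- *Research agenda of the current study (stigma-II)* gives a timing for the whole set: "The primary and secondary outcomes will be measured directly pre- and post-intervention", and again at the 3- and 6-month follow-ups. The sentence after it reads: "The primary outcome “help-seeking behaviour” will be assessed at the subsequent follow-ups". Behaviour is the only outcome that the article labels primary.
- *Primary research questions* lists H1, H2a to H2c and H3a to H3c. The first reads: "The agreement with a biopsychosocial- vs. a mono-causal model leads to a higher help-seeking intention". The third begins: "Positive treatment experience is associated positively with both self-efficacies (H3a", and goes on to intention (H3b) and behaviour (H3c).
- *Outcome measures*, Table 2, has a row "Help-seeking behaviour/ health-care utilisation" marked at T2 and T3 only. Help-seeking intention and both self-efficacy scales are marked at T0, T1, T2 and T3.

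*Power & sample size* bases N = 840 on a repeated-measures ANOVA, within-between interaction, with f = 0.10, 24 groups, power 0.95 and "A significance level of α = 0.05". It does not say which outcome this is for, how many measurements it assumes, or how they are correlated.

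**The concern.** The label *primary* points to different variables in adjacent sections. A measurement before and after the intervention is possible for intention and self-efficacy but not for behaviour, so the general timing sentence cannot be true of the one outcome that is named as primary. Most of the primary hypotheses then concern other endpoints.

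Two things are at stake. First, a reader cannot tell which result answers the title question of whether utilisation of help improves. Intention cannot simply stand in for it: the article reports from the earlier project that intention explained 22–37% of the variance in behaviour. H2a even predicts lower intention to seek professional help, although the same section opens by expecting the intervention to raise intention and utilisation. Second, the power statement reads as covering the study's main question, yet its form fits a different outcome from the one named as primary.

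**Working it through.** **Step 1. Endpoint of each primary hypothesis** (*Primary research questions*, with timing from Table 2)

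| Hypothesis | Endpoint | Measured at T0 and T1? | Predictor |
|---|---|---|---|
| H1 | intention | yes | agreement with a causal model |
| H2a | intention | yes | self-efficacy to help oneself, enhanced |
| H2b | intention | yes | self-efficacy to seek professional help, enhanced |
| H2c | behaviour | no | self-efficacy to seek professional help, enhanced |
| H3a | both self-efficacies | yes | past treatment experience |
| H3b | intention | yes | past treatment experience |
| H3c | behaviour | no | past treatment experience |

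Intention 4, self-efficacy 1, behaviour 2. So 5 of 7 do not test the named primary outcome (6 of 8 if H3a is counted once per scale). Past treatment is not allocated, which leaves H2c as the only primary hypothesis about an intervention effect on behaviour.

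**Step 2. The plan's own sample size**

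Inputs from *Power & sample size*: k = 24 groups, f = 0.10, α = 0.05, power 0.95. Assumed because not stated: m = 2 measurements, correlation ρ = 0.5, sphericity ε = 1.

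For the within-between interaction:
- λ = f²·N·m/(1 − ρ) = 0.01 × 840 × 2/0.5 = 33.6
- df1 = (k − 1)(m − 1) = 23
- df2 = (N − k)(m − 1) = 816

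Power from the noncentral F is 0.954. The smallest N reaching 0.95 is 825, which rounds up to 24 equal groups of 35, N = 840. The stated figure is reproduced.

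Other settings tried do not reproduce it: m = 3, ρ = 0.5 gives 720; m = 4, ρ = 0.5 gives 648; m = 4, ρ = 0.3 gives 888; m = 2, ρ = 0.3 gives 1152. Two measurements with ρ = 0.5 is therefore a plausible reconstruction but remains an inference.

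**Step 3. Does that calculation describe behaviour?**

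A group-by-time interaction reflects an intervention effect when one time point precedes the intervention. Behaviour is measured only at T2 and T3, both afterwards. An interaction over those two would test whether the groups change differently between 3 and 6 months. A constant difference between groups at both follow-ups would not show up in it.

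**Step 4. Power at one follow-up with the same f = 0.10**

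Here λ = f²·N. At N = 840 that is 8.4, against 33.6 above: the factor m/(1 − ρ) = 4 is lost.

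| Comparison | df1 | N = 840 (λ = 8.4) | N = 960 (λ = 9.6) |
|---|---|---|---|
| All 24 groups | 23 | 0.30 | 0.35 |
| Professional-help factor, 3 levels | 2 | 0.74 | 0.80 |

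The error df is N − 24. In Table 1 the professional-help module is absent in 8 groups, text in 8 and video in 8, so the three levels are balanced.

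**Step 5. If behaviour is analysed as yes/no** (an assumption)

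At N = 960 the split is 8 × 40 = 320 without the module and 16 × 40 = 640 with it. For a rise of 5 percentage points, power falls from 0.58 at an assumed rate of 10% without the module to 0.33 at an assumed 33%.

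**The case against.** The fairest defence is that intention and behaviour are both meant as primary. The timing sentence uses the plural, the next sentence can be read as the exception for behaviour, *Primary research questions* opens by naming both, and Table 2 fits that reading. On it, an intention result reported as primary contradicts nothing. This reading is possible, but the article labels one outcome primary, in the singular, and never gives intention that label. H3a, on self-efficacy, would remain outside even this wider set.

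A reader might go further and infer that the trial will claim primary success without any effect on behaviour, or that its false-positive risk is about 18.5% (1 − 0.95⁴), 30.2% (1 − 0.95⁷) or 33.7% (1 − 0.95⁸). The documents do not support either inference. They state no success rule, and alpha allocation, ranking of hypotheses and the choice between T2 and T3 may sit in an analysis plan that is not shown. The error rates also assume independent tests, although four hypotheses share the intention endpoint. The four-test figure counts H1 as a randomised comparison, although H1 is worded as agreement with a causal model and *Intermediary process measures* assigns a measured list of causes to it. These rates are illustrative only.

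It is also true that the article does not state the number of measurements behind N = 840, and that self-efficacy has pre- and post-intervention values as well as intention. The calculation cannot be tied to intention alone. What stands is that it does not describe an intervention effect on behaviour.

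**Conclusion.** The inconsistency is real and lies in what the article states, not in detail left to another document. An unseen analysis plan could set a hierarchy, but it could not make the two adjacent timing sentences agree or change which endpoints the article lists under its primary hypotheses.

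In size, five of seven primary hypotheses do not test the named primary outcome, and one concerns an intervention effect on it. The stated power of 0.95 does not carry over to behaviour: at one follow-up it is 0.74 to 0.80 for the professional-help factor and 0.30 to 0.35 for all 24 groups. These figures assume that f = 0.10 keeps its value when the test changes and that behaviour is analysed as a continuous score; the yes/no figures rest on assumed rates. The reconstruction of N = 840 assumes m = 2 and ρ = 0.5.

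It would go too far to say that H2c must be the sole primary test. That is one coherent choice among several. The point should be corrected, but it does not invalidate the design.

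**What to change.** Reconcile *Research agenda*, *Primary research questions* and *Power & sample size* by one of two routes.

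- **(a) Behaviour stays primary.** Name the follow-up, make H2c its confirmatory test, label the intention and self-efficacy hypotheses key secondary, and limit the pre/post timing sentence to the outcomes it fits. Restate power for that comparison: about 0.74 at N = 840 and 0.80 at N = 960 under the assumptions above.
- **(b) Intention becomes primary, or co-primary with behaviour.** Say so explicitly, share or order alpha between them if both are primary, and state that the 0.95 applies to the pre/post outcome only.

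In both cases label H3 as associational. If the registry entry, which is not shown, differs from the chosen wording, update it with a date.

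The cost is a rewording of three sections and a new power statement, with no added data collection. The downside is that under (a) some hypotheses lose primary status and the stated power falls; keeping 0.95 for behaviour would need more participants or a larger assumed effect. Under (b) the headline power no longer covers behaviour, and sharing alpha costs some power.

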#### Primary research questions

The intervention is expected to directly and indirectly influence help-seeking intention and behaviour positively, resulting in a higher intention as well as higher rates of professional health care utilisation. Our primary research questions are:
Does a biopsychosocial causal model of depression make it easier to articulate an intention to seek health care treatment?H1: The agreement with a biopsychosocial- vs. a mono-causal model leads to a higher help-seeking intention.Does the strengthening of context-specific self-efficacy (self-efficacy to help oneself and to seek professional help) influence treatment intention or utilisation?H2: Enhancing self-efficacy to help oneself leads to less intention to seek professional help (H2a), whereas enhancing self-efficacy to seek professional help leads to higher help-seeking intention (H2b) and help-seeking behaviour (H2c).What importance does previous treatment experience have for the development of both self-efficacies and the last stages of the process of help-seeking?H3: Positive treatment experience is associated positively with both self-efficacies (H3a), help-seeking intention (H3b) and behaviour (H3c).

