#### Secondary research questions

The intervention is expected to influence different stigmatising attitudes and self-identification as mentally ill. Our secondary research questions are:
4.Does a conception of depression as a manifestation on a mental health-illness continuum favour the readiness for self-identification as mentally ill? Does it also have a reducing effect on stigmatising attitudes?H4: The agreement with continuum beliefs leads to higher self-identification (H4a) and reduces stigmatising attitudes (H4b).5.Does the strengthening of mental health literacy have a reducing effect on stigmatising attitudes and favour the readiness for self-identification as mentally ill?H5: The strengthening of mental health literacy leads to a higher self-identification (H5a) and reduces stigmatising attitudes (H5b).6.Can a biopsychosocial causal model of depression have a reducing effect on stigmatising attitudes? Does it also favour the readiness for self-identification as mentally ill?H6: The agreement with a biopsychosocial causal model leads to a higher self-identification (H6a) and reduces stigmatising attitudes (H6b).7.What importance does previous treatment experience have for the readiness for self-identification as mentally ill and the expression of stigmatising attitudes?H7: Positive treatment experience is associated positively with self-identification (H7a) and negatively with stigmatising attitudes (H7b).

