## Methods/design

A fractional factorial design is chosen, due to the number of influenced variables and the complexity of the study. This type of design will allow for an economic assessment, reducing the number of groups needed while ensuring that sufficient data for the primary and secondary outcomes can be collected. The conditions are systematically varied to determine the necessary within group condition-combinations after calculating the number of groups needed by multiplying the cartesian products of the variables with two and three levels, respectively: x = 3^2^ * 2^3^ = 72 (i.e., full factorial design). Fractioning the design by subtracting a variable-factor from the three-level variable resulted in our design (see Table 1) with a resolution of V and, therefore, being able to differentiate between main effects and two- (three-) way interactional effects: x = 3^2–1^ * 2^3^ = 24. For more information on fractional factorial designs refer to Dean et al. [15] and Siebertz, van Bebber, and Hochkirchen [55].

**Table 1 Tab1:** Fractional factorial design with 24 groups

Experimental group	Intervention content				
	Continuum belief	Mental health literacy	Causal belief	Self-efficacy (self-help)	Self-efficacy (treatment)
1 (control group)					
2				T	T
3		T			T
4		T		T	V
5			T		T
6			T	T	V
7		T	T		V
8		T	T	T	
9	T				T
10	T			T	V
11	T	T			V
12	T	T		T	
13	T		T		V
14	T		T	T	
15	T	T	T		
16	T	T	T	T	T
17	V				V
18	V			T	
19	V	T			
20	V	T		T	T
21	V		T		
22	V		T	T	T
23	V	T	T		T
24	V	T	T	T	V

*Note.* T = text-based intervention, V = video-based intervention. Information for both intervention-types are the same. The groups are determined through a priori systematic variation and fractioning of the condition-combinations. The design has a resolution of V and can statistically differentiate between main and two- (three-) way interactional effects

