#### Intermediary process measures

With a new scale, taken and adapted from different measurements (considering the meta-analysis of [42]) continuum belief of mental illness is assessed. Participants are asked whether they agree with the statements (e.g., “Now and again most of us have symptoms of a mental illness”) on a 5-point Likert scale from 1 = “don’t agree at all” to 5 = “I agree completely”. Final reliability scores will be calculated with the data. This instrument will be used to test the hypothesis H4.

With a short form of the *Depression Literacy Scale* [20] depression literacy is assessed. Participants are asked whether a statement (e.g., “Too little or too much sleep can be a sign of depression”) is 1 = “true”, 2 = “false”, or 3 = “don’t know”. Based on secondary data analysis, the reliability score for the short-form is α = .72. This instrument will be used to test the hypothesis H5.

With a list of possible causes [51] causal belief is assessed. Participants are asked whether they believe a listed cause (e.g., “Living in a big city”) is a cause for their complaints on a 5-point Likert scale from 1 = “definitely is not a cause” to 5 = “definitely is a cause”. This instrument will be used to test the hypotheses H1 and H6.

Self-efficacy is assessed with context-relevant adaptations of items taken from the BRAHMS-Study [43] and a study assessing the health care use of homeless people [23]. Concerning self-efficacy for self-help, participants are asked to rate how certain they are that they can overcome specific barriers (e.g., “… if my complaints don’t get better despite my efforts”) on a 5-point Likert scale from 1 = “very uncertain” to 5 = “very certain”. Concerning self-efficacy for seeking professional help, participants are asked to rate how confidant they are that they can overcome barriers of the health care system (e.g., “I am able to deal with long waiting times”) on a 5-point Likert scale from 1 = “not confident” to 5 = “very confident”. Final reliability scores for both of these adapted instruments will be calculated with the data. These instruments will be used to test the hypotheses H2 and H3.

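### H1, H4 and H6 state causal effects of measured agreement, which is not randomised, and H1's mono-causal comparator matches no condition in the design

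*Protocol article*

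**What the plan says.** Under Primary research questions, the Protocol article states "H1: The agreement with a biopsychosocial- vs. a mono-causal model leads to a higher help-seeking intention". Under Secondary research questions, H4 and H6 have the same structure: agreement with continuum beliefs, or with a biopsychosocial model, is said to raise self-identification and lower stigma. For example: "H4: The agreement with continuum beliefs leads to higher self-identification (H4a) and reduces stigmatising attitudes (H4b").

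The wording differs where the exposure is openly not randomised: "H3: Positive treatment experience is associated positively with both self-efficacies (H3a), help-seeking intention (H3b) and behaviour (H3c"). H7 is worded in the same way. H2 and H5 speak of enhancing or strengthening something, which describes what an intervention does.

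Intermediary process measures links the participant-rated list of causes to two of these hypotheses ("This instrument will be used to test the hypotheses H1 and H6") and the continuum scale to the third ("This instrument will be used to test the hypothesis H4"). On the list of causes, "Participants are asked whether they believe a listed cause (e.g., “Living in a big city”) is a cause for their complaints".

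In Table 1 (Methods/design) the causal-belief column holds only T or a blank, and the continuum column holds blank, T or V. The note reads "T = text-based intervention, V = video-based intervention. Information for both intervention-types are the same". The control group sees the case vignette alone.

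**The concern.** Randomisation protects comparisons between people who were and were not given a piece of material. It does not protect comparisons between people who do and do not agree with a belief. Agreement after the intervention reflects what a person believed beforehand, their severity, their education and their treatment history, and these can also move intention and stigma. The article's own model (Background) says that previous treatment experience acts on the intermediary variables and is also directly associated with help-seeking behaviour. H3b expects an association with intention as well. That is a common cause named by the plan itself.

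For H1 there is a further mismatch. Its comparator is a mono-causal model, but the design's comparator is no causal-belief material. At stake is whether a primary question gets a randomised answer, which the data can give, or an association reported as an effect.

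**Working it through.** **1. The plan's own figure.** Power & sample size gives f = 0.10, α = 0.05, power 0.95, 24 groups and N = 840 for a repeated-measures within-between interaction. The number of measurements m and their correlation ρ are not stated. With λ = f²·N·m/(1−ρ), df1 = 23(m−1), df2 = (N−24)(m−1), and assuming m = 2 and ρ = 0.5:
- The smallest sufficient N is 825, which rounds up to 840 = 24 × 35.
- At N = 840, λ = 0.01 × 840 × 2/0.5 = 33.6, df = 23 and 816, power = 0.9545.
- Other values do not give 840: m = 3 or 4 with ρ = 0.5 gives 720 or 648; m = 2 with ρ = 0 or 0.7 gives 1632 or 504.

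So the trial is sized on a test of the randomised groups.

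**2. What Table 1 randomises.**
- Causal belief: T in 12 groups (5–8, 13–16, 21–24), blank in 12. Each half contains every level of the other factors equally often (6/6 groups for two-level factors, 4/4 for three-level factors). There is no mono-causal level.
- Continuum belief: blank, T and V in 8 groups each.

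H6 and H4 therefore have a randomised comparator (no material). The comparator stated in H1 does not exist as a condition.

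**3. Power of the randomised contrasts.** At 40 per group, causal text versus none is 12 × 40 = 480 versus 480. For two equal groups d = 2f = 0.2.
- Post-only: d·√(n/2) = 0.2 × √240 = 3.098; power = Φ(3.098 − 1.96) = 0.873. At 35 per group (420 versus 420) it is 0.826.
- Adjusted for the T0 value: divide by √(1−ρ²). With ρ assumed, 3.098/√0.75 = 3.578 at ρ = 0.5, power 0.947. At ρ = 0.3 it is 0.901 and at ρ = 0.7 it is 0.991.
- On the interaction scale of step 1, two groups and N = 960 give λ = 0.01 × 960 × 2/0.5 = 38.4 and power above 0.999. There f = 0.10 means a 0.4 SD difference in change (0.4 × √240 = 6.197, and 6.197² = 38.4), so this is not the same effect as d = 0.2.
- Continuum content versus none, 640 versus 320, d = 0.2, post-only: 0.2/√(1/640 + 1/320) = 2.921; power = 0.832.

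**4. The risk if agreement is the regressor (illustration).** Assumptions: N = 960, the text shifts agreement by 0.2 SD, there is no true effect on intention, and the analysis is unadjusted. The documents give no value for the confounded correlation r, so a range is shown, from 2,000 simulated trials each.

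| Confounded r | Rejections, measured agreement | Rejections, randomised text |
|---|---|---|
| 0 | 5% | 5% |
| 0.05 | 34% | 4% |
| 0.10 | 87% | 5% |
| 0.20 | 100% | 5% |

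The approximation Φ(r√957 − 1.96) agrees: r = 0.05 gives Φ(−0.41) = 0.34 and r = 0.10 gives Φ(1.13) = 0.87. A shift of 0.2 SD explains 0.01/1.01, about 1%, of the variance in agreement. Under these assumptions almost all variation in agreement is not randomised.

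**The case against.** A reader might infer that the tests abandon the randomised factors. The article does not show that. Statistical methods lists correlation, regression, repeated-measures multivariate analysis of variance, multilevel and path models without assigning any to a hypothesis. The one test fixed numerically uses the 24 groups. Nor does naming a scale as a test instrument fix its role: the same phrase is used for outcomes such as self-identification and intention, and for the self-efficacy and literacy scales under H2 and H5, which are worded as manipulations. The role could be exposure, mediator or manipulation check.

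The introduction to the primary questions also speaks of direct and indirect effects of the intervention, and the research agenda places beliefs between intervention and outcome. Mediation is a fair reading, and path models are planned. In addition, T0 values of the beliefs and outcomes are collected, so an adjusted analysis could reduce the confounding shown above.

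All of this stands, and it limits the point. It does not remove it. The hypotheses themselves name agreement as the cause, and in a mediation model the path from agreement to outcome is still not randomised. Baseline adjustment covers only what was measured. No reading supplies H1 with a mono-causal arm. The intervention texts are in a supplement that was not available, but a text shown to one half of the groups cannot create a mono-causal condition in the other half.

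**Conclusion.** The point holds as a mismatch between hypotheses and design. H1, H4 and H6 attach causal verbs to a measured belief, while the sample size rests on randomised groups, so it is not settled which effect is to be tested. For H1, which is primary, the comparator is also absent from the design. That absence does not extend to H4 (none, T, V) or H6 (T, none).

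This is more than detail left to an analysis plan, because the exposure and comparator that the article does state do not fit what is allocated. It is not a finding that the planned tests ignore randomisation.

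The false-positive rates are conditional on an assumed confounded correlation and no adjustment; they show sensitivity and are not a forecast. The power of about 87% for the causal-text contrast assumes 480 per side and d = 0.2. Power is higher with baseline adjustment, by an amount that depends on ρ, which the article does not give.

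**What to change.** - State H1 and H6 as the effect of the randomised causal-belief text versus none, on intention (H1) and on self-identification and stigma (H6).
- State H4 as the effect of continuum content (text or video) versus none.
- Test each in a model containing the randomised factors and the T0 value of the outcome.
- Remove the mono-causal comparison from the confirmatory H1.
- Label analyses of the agreement scales, including any biopsychosocial versus mono-causal comparison, as manipulation checks, mediation or associational analyses.
- Leave H3 and H7 as they are; they are already worded as associations.

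The cost is rewording three hypotheses and specifying their model. No new data, groups or participants are needed.
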